### Statistical methods

This study is exploratory to provide necessary data for sample size considerations for a possible subsequent pivotal trial. Sample size considerations are based on research by Emre et al. [12]; they found a 2.1 ± 8.2 point improvement on ADAS-cog with rivastigmine treatment compared to a worsening of 0.7 ± 7.5 points with placebo after 24 weeks (baseline 23.8 ± 10.2 points). Clearly, such small mean differences in combination with comparatively large standard deviations shown by the rivastigmine study will be only be detectable with appropriate power with sample sizes (2*125 = 250) far above that planned for our study. However, we hope to encounter considerably larger effects for NBM-DBS. Within this purely explorative analysis, we will test the null hypothesis of equal mean ADAS-cog change scores from V1 to V2 for both study treatments (STN-DBS + NBM-DBS versus STN-DBS + sham NBM-DBS) by a Type III F-test within an analysis of covariance (ANCOVA), with baseline ADAS-cog as covariate. Assuming a small-to-moderate correlation between baseline ADAS-cog and ADAS-cog change score from V1 to V2, a sample size of 2*6 = 12 patients ensures a power of 80% to detect a standardized mean difference of 1.66 as significant deviation from the null hypothesis of equal mean change scores for both treatments at significance level 0.05. This means we will be able to detect only large effects as significant, but that is not the main objective of this pilot study.

Note that because of the small sample size, statistical testing will not be the focus of data analysis. Despite the known robustness of ANCOVA, it may be difficult to detect violations in ANCOVA assumptions. A critical issue comes from possible differences in the sample distributions of baseline variables between the two treatment groups when comparing mean change scores for endpoints. If appropriate mean change scores resp. distributions of change score will be compared without adjustment for baseline variables by the two-sided T-test resp. by the Mann-Whitney test instead of an F-test within ANCOVA.

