**Methods:**

We aim to include 12 patients with mild-to-moderately severe PDD who fulfill indication criteria regarding motor symptoms for STN-DBS. Eligible patients will undergo implantation of a neurostimulation system with bilateral electrodes in both the STN and NBM. After 12 weeks of STN-DBS (visit 1/V1), participants will be randomized to receive either effective neurostimulation of the NBM (group 1) or sham stimulation of the NBM (group 2). NBM-DBS will be activated in all participants after 24 weeks of blinded treatment (visit 2/V2). The primary outcome will be the safety of combined bilateral STN- and NBM-DBS, determined by spontaneously-reported adverse events. Other outcome measures will comprise changes on scales evaluating cognition, activities of daily living functioning and clinical global impression, as well as motor functions, mood, behavior, caregiver burden and health economic aspects, and several domain-specific cognitive tests. Changes in scores (V1 – V2) for both treatment arms will undergo analysis of covariances, with baseline scores as covariates.

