**Fig. 1 Fig1:**
[figure not shown]
Visit schedule of DEMPARK-DBS: Icon “flash” = ‘activation’ or ‘active’ DBS. PREBASE, presurgical baseline visit; POSTBASE, postsurgical baseline visit; SCR, screening visit; V1, Visit 1; V2, Visit 2; V3, Visit 3

During the screening visit, the PDD diagnosis will be confirmed by the Movement Disorders Society (MDS) criteria using the algorithm for PDD at level I [11]. The MMSE total score must lie between 10 and 24 points, indicating mild-to-moderately severe dementia. Patients will fulfill clinical inclusion criteria for STN-DBS in terms of motor scores and requirements for local/general anesthesia.

The preoperative baseline examination will be performed 4 weeks prior to the DBS operation. Table 2 shows the full data set to be collected at pre- and postoperative Baseline and Visits 1–3 to achieve exploratory study endpoints, and includes assessment of motor function in the medication-“off” state after 12-h withdrawal of dopaminergic medication and medication-“on” state after standard levodopa challenge; video recording will also be used for documentation. All other scores and scales will be performed in the medication-“on” state, to assess global cognitive function, neuropsychiatric symptoms, and a number of domain-specific tests as part of a detailed neuropsychiatric battery, as well as quality of life, health economics, and caregiver burden. During all study visits, adverse events will be documented and rated for frequency and severity.

**Table 2 Tab2:** Data set: assessment at presurgical/postsurgical baseline, visits 1–3

Motor assessments	• Movement Disorder Society-Unified Parkinson’s Disease Rating Scale (MDS-UPDRS) III (medication-off/−on state) • MDS-UPDRS I, IV • Clinical Dyskinesia Rating Scale (CDRS)
Global cognitive function	• Alzheimer’s Disease Assessment Scale, cognitive subscale (ADAS-cog)
Activities of daily living	• Alzheimer’s Disease Cooperative Study, Activities of Daily Living (ADCS-ADL) • MDS-UPDRS II
Neuropsychiatric symptoms	• Beck Depression Inventory (BDI) II, • Starkstein Apathy Scale • Neuropsychiatric inventory (NPI)
Domain specific (frontal executive) tests	• Delis-Kaplan Executive Function Systems (D-KEFS) verbal fluency battery • Wisconsin Card Sorting Test (modified version) • Trail Making Task (TMT) Part A + B • Stroop Test (Victoria Version) • Symbol Digit Modalities Test (SDMT)
Domain specific (attention) test	• Brief Test of Attention (BTA)

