Twelve weeks after STN activation, neurostimulation Visit 1 (V1) will take place. At this time, baseline evaluation of the clinical global impression of change (ADCS-CGIC) will be performed by a blinded rater not involved in medical treatment and with no information about the results of other scales and scores. For the first baseline interview with the patient and caregiver, documented medical history will be the only additional information that may be studied. Motor assessments will be performed in the medication-“off” and -“on” state with active STN-DBS; all other scales and scores will be evaluated in the medication-“on” state with active STN-DBS. Subsequently, medication and STN-DBS parameters will be optimized if necessary, followed by 1:1 blinded randomization to active or sham NBM-DBS. After another 24 weeks, Visit 2 (V2) will take place. To evaluate CGIC compared to V1, patient and caregivers will be re-interviewed by the blinded rater that performed the baseline interview. This time, no additional information may be provided from medical records or other information sources. Motor assessments will be performed in the medication-“off” and -“on” state with active STN-DBS and active or sham NBM-DBS; all other scales and scores will be evaluated in the medication-“on” state with active STN-DBS and active or sham NBM-DBS. Subsequently, STN-DBS will be adapted if necessary and active NBM-DBS continued in all patients. Visit 3 (V3) will be performed 48 weeks after activation of NBM-DBS in both patient groups, i.e., 24 weeks after V2 in the NBM-DBS group, 48 weeks after V2 in the sham NBM-DBS group. The CGIC will again be rated compared to V1. After V3, the study will end and medication, STN-DBS, and NBM-DBS will be adjusted without restrictions according to clinical needs. An annual follow-up visit for up to 5 years after activation of NBM-DBS will be provided to all participants.

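### The fallback lets an unadjusted t-test or Mann-Whitney test replace the baseline-adjusted ANCOVA after the data are seen, although neither reason hinted at (baseline imbalance, doubtful assumptions) justifies dropping the baseline score

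*Protocol article*

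**What the plan says.** The Abstract states that V1-to-V2 change scores "will undergo analysis of covariances, with baseline scores as covariates". The Statistical methods section repeats this for ADAS-cog as an F-test within ANCOVA, and assumes a small-to-moderate correlation between baseline and change, without a number. The power claim rests on that analysis: with 12 patients and testing at the 5% level, the stated power is 80% for a standardized difference of 1.66 in mean change.

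The next paragraph first says that violations of the ANCOVA assumptions may be hard to detect, and then: "A critical issue comes from possible differences in the sample distributions of baseline variables between the two treatment groups". The sentence after that provides the fallback, in which change scores or their distributions are "compared without adjustment for baseline variables by the two-sided T-test resp. by the Mann-Whitney test instead of an F-test within ANCOVA". The only condition is that this be appropriate. Nothing says who judges that, on what evidence, or how to choose between the two unadjusted tests.

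The covariate is called baseline with no visit attached. The Fig. 1 legend gives that name to two earlier visits ("PREBASE, presurgical baseline visit; POSTBASE, postsurgical baseline visit") and lists V1 separately. Table 2 and the study description also use the word for V1, but only for the CGIC interview. Randomization takes place after the V1 assessments ("followed by 1:1 blinded randomization to active or sham NBM-DBS").

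**The concern.** Chance baseline imbalance is a reason to keep a covariate. A change score removes a baseline difference only when change is unrelated to baseline, and the plan itself assumes that it is related. If the fallback is used when the arms differ at V1, part of the difference in mean change reflects where the arms started.

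The other possible motive, doubtful ANCOVA assumptions, supports a rank-based or permutation method. Such methods can still adjust for baseline, so this motive does not justify dropping the score either.

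Leaving three tests open without a rule also lets the analysis depend on the data. The main thing at stake is the estimate: the section says the study is meant to supply data for sizing a possible pivotal trial, and a 12-patient trial has only its own realized imbalance.

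The unnamed covariate visit adds to this. Stimulation of the STN starts after the postsurgical baseline, and medication may be changed after surgery. An earlier score is therefore not the value from which change is measured.

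**Working it through.** **Inputs from the article.** 6 per arm, 1:1; standardized difference 1.66; significance level 0.05; stated power 80%. From the cited rivastigmine trial: change SDs 8.2 and 7.5, baseline SD 10.2, difference in change 2.1 + 0.7 = 2.8 points.

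**Assumptions.** Normal data. The size r of the baseline-change correlation is not given, so values from 0 to about 0.4 are shown.

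**1. The plan's own figures.**
- Pooled change SD = √((8.2² + 7.5²)/2) = 7.86. Detecting 2.8 points with 80% power needs 124 per arm by formula, and 125 per arm gives 80.1%. The article's 2*125 is reproduced.
- ANCOVA power from the noncentral t with 9 df and effect 1.66/√(1 − r²): 76.5% at r = 0.3, 79.7% at r = 0.40, and 80% at r ≈ 0.41. The stated 80% is reproduced with adjustment at that correlation.
- Unadjusted two-sided t-test (10 df) at 1.66: 73.6%. The stated power does not carry over to the fallback.

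**2. How common imbalance is.** The SE of the difference in baseline means is √(2/6) = 0.577 SD. The chance of a gap larger than this is 2 × (1 − Φ(1)) = 32%. At SD 10.2 the threshold is 0.577 × 10.2 = 5.9 ADAS-cog points. The mean gap beyond it is 0.577 × φ(1)/(1 − Φ(1)) = 0.88 SD. Gaps above 1 SD occur in about 8% of trials.

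**3. Conditional bias of the unadjusted change difference.** Given the gap, the bias is r × gap, in SDs of change.

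| r | Bias, gap > 0.58 SD | In points (× 7.86) |
|---|---|---|
| 0.3 | 0.3 × 0.88 = 0.26 | 2.1 |
| 0.41 | 0.41 × 0.88 = 0.36 | 2.8 |

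The ANCOVA estimate has bias of about 0 in the same trials.

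**4. Type I error, from simulated null trials.**
- t-test given a gap above 0.58 SD: about 6.3% at r = 0.3 and 7.3% at r = 0.41.
- t-test given a gap above 1 SD: roughly 8% and 11%.
- ANCOVA: about 5% throughout.
- Overall, if the t-test replaces ANCOVA only when imbalance is seen: 5.1-5.8%.
- Worst case, significance by any of the three tests: 6.8% at r = 0, rising to about 7.5% at r ≈ 0.4.

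**5. Accuracy (mean-squared error).** Let d be the gap in SDs and take the change variance as 1. The unadjusted estimate has error r²d² + (1 − r²)(2/6). ANCOVA has (1 − r²)(2/6 + d²/8), because the slope is estimated from 10 within-group df and 1/(10 − 2) = 1/8. ANCOVA is better when (1 − r²)/8 < r², that is r² > 1/9 or r > 0.33, whatever the gap. For gaps above 0.58 SD, the root-mean-squared errors (unadjusted vs ANCOVA) are 0.616 vs 0.633 at r = 0.3 and 0.648 vs 0.605 at r = 0.41.

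**The case against.** **The trigger is inferred.** A reader might conclude that the plan orders adjustment to be dropped whenever the arms differ at baseline. The text does not say so. The link is that one sentence follows the other, and difficulty with ANCOVA assumptions is mentioned just before. This stands, which is why the point is put as a fallback that neither motive justifies.

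**ANCOVA pays in variance.** With 12 patients and a small correlation, the unadjusted estimate has the lower mean-squared error even in imbalanced trials. Once chance imbalance is allowed for, power at 1.66 is 69.9% for ANCOVA against 73.8% for the t-test at r = 0.2, and 72.0% against 73.6% at r = 0.3. This also stands. It would be wrong to say that adjustment is always more accurate here. But the plan's 80% is reached at r ≈ 0.41, where ANCOVA is ahead on mean-squared error. If the correlation is thought smaller, that argues for choosing the unadjusted test in advance, not for switching to it afterwards.

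**The harm to error rates is small.** Conditional bias has either sign and averages to zero over trials, and the standard error of the difference is itself about 0.577 × 7.86 = 4.5 points. The 7-7.5% figure supposes that any of the three tests may be taken as the result, which the article does not propose. It is an upper bound.

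**Detail may sit in the analysis plan.** Switching criteria and the covariate visit could be set there, and their absence from an article would not by itself be a finding. But the article does state the fallback, and what it states is an unadjusted analysis.

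**V1 is also called a baseline.** It would be wrong to say that only the two earlier visits carry that name. V1 does too, for the CGIC, and it is the natural reading for a V1-to-V2 change. What remains is a request to name it.

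**Conclusion.** The concern holds at moderate severity. The plan names baseline differences as critical and then permits, on a vague condition, an analysis that ignores them. In the roughly one trial in three with a gap above 0.58 SD, the unadjusted ADAS-cog difference carries a bias of about 2.1 to 2.8 points at r = 0.3 to 0.41. That is close to the whole 2.8-point rivastigmine difference that the plan cites, and the t-test's conditional type I error is 6.3-7.3%. These figures rest on normal data, the assumed correlations and SDs borrowed from the rivastigmine trial.

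Three stronger conclusions are not supported. The 80% power figure is not an error: it is reproduced for the adjusted analysis. The fallback does not seriously inflate the overall type I error. No primary conclusion depends on it: safety is the primary endpoint, ADAS-cog is exploratory, and the article says that testing is not the focus. The gain from keeping adjustment lies in conditional bias, error control and a fixed analysis, not in guaranteed precision.

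**What to change.** - Pre-specify ANCOVA of the V1-to-V2 change, with the V1 score of the same scale as covariate, as the single main analysis, kept whatever baseline imbalance is observed. The CGIC is rated as change from V1 and has no V1 score of its own, so it needs a separate line.
- If the ANCOVA assumptions look doubtful, take the p-value from a re-randomization test of the adjusted difference (12!/(6! × 6!) = 924 allocations if 6/6 is the only restriction), or use rank ANCOVA.
- Report the unadjusted t-test and Mann-Whitney test only as labelled sensitivity analyses.

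This takes two or three sentences and no new data, since Table 2 already schedules these scales at V1. The price is slightly lower precision if the baseline-change correlation turns out to be small (below about 0.33).

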### Perspective

DEMPARK-DBS will be the first controlled study to evaluate combined STN-NBM-DBS using four electrodes as originally described by Freund et al. [14]. We will assess the feasibility and safety of combined STN-NBM-DBS in patients with PDD and will determine whether additional NBM-DBS improves or slows the progression of cognitive decline. Positive results would provide a basic concept for future studies evaluating the efficacy of NBM-DBS in larger PDD cohorts.

Dopaminergic treatment may worsen cognitive functions in advanced PD [25], and has a number of side effects that amplify behavioral disorders also primarily caused by dementia. STN-DBS allows a significant reduction in dopaminergic medication; by reducing associated hyperdopaminergic cognitive and behavioral disorders, it could benefit PDD patients. Proof-of-safety of STN-DBS in PDD might also have an impact on the general selection criteria for DBS in patients with advanced PD.

## Data Availability

Not applicable.

## Abbreviations

Ach: Acetylcholine
AChE: Acetylcholinesterase
ADAS-cog: Alzheimer’s Disease Assessment Scale, cognitive subscale
ADCS-ADL: Alzheimer’s Disease Cooperative Study, Activities of Daily Living
ADCS-CGIC: Alzheimer’s Disease Cooperative Study, Clinical Global Impression of Change
ADL: Activities of daily living
BDI: Beck Depression Inventory
BSC: Boston Scientific Corporation
BTA: Brief Test of Attention
CAT: Cholineacetyltransferase
CDRS: Clinical Dyskinesia Rating Scale
DBS: Deep brain stimulation
D-KEFS: Delis-Kaplan Executive Function Systems
EQ-5d: EuroQol
MCI: Mild cognitive impairment
MDS: Movement Disorder Society
MMSE: Mini-Mental State Examination
NBM: Nucleus basalis of Meynert
NPI: Neuropsychiatric Inventory
PD: Parkinson’s disease
PDD: Parkinson’s disease dementia
PDQ: Parkinson’s Disease Questionnaire
PET: Positron Emission Tomography
QALY: Quality-adjusted life year
SDMT: Symbol Digit Modalities Test
SF: Short Form (SF-36)
STN: Subthalamic nucleus
TMT: Trail Making Task
UPDRS: Unified Parkinson’s Disease Rating Scale
ZBI: Zarit Burden Interview
